# 8. Sample size calculations and statistical analysis plan

In a validation-trial of ReDS, Amir et al investigated 16 patients with acute heart failure and found a mean fluid content of 39.8 + 6.8 % [25]. Similar results were seen when estimating fluid content by the chest CT, which is regarded as the gold standard.

To have 90 % power to find a difference of 4 % in lung fluid content (change from 39.8% to 35.8%) with a standard deviation of 6.8, we need to include 122 patients (61 in each group). The α-level is 0.05, and the beta is 10%. We expect minimal dropouts. The study will include patients over an estimated period of 1 years in two centers. We will include patients until we have reached the estimated sample size without any missing values in the primary outcome, to ensure that we can conclude on our primary hypothesis.

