# 7. Outcomes

## 7.1 Primary outcome

## Pulmonary parenchymal fluid content measured by ReDS after 24 hours preceded by 10 minutes without oxygen-supplementation.

## 7.2 Secondary outcomes

1. Arterial blood gas concentration after 24 hours preceded by 10 minutes without oxygen-supplementation.
2. All-cause mortality at day 30
3. Days alive out-of-hospital to day 30
4. Time to freedom from oxygen-supplementation

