# 12. Statistical analyses plan

Baseline characteristics and outcomes of the patients in the groups will be compared individually. The primary exposure variable is allocation to the intervention group compared to control group. Categorical variables will be presented as numbers (frequencies) and compared with the Chi-Squared or the Fisher’s exact test, as appropriate, whereas continuous variables will be presented as mean ±SD if normally distributed, and as median (25^th^ percentile-75^th^ percentile) if non-normally distributed and compared with the T-test. In continues data, there are non-normally distributed, logarithmic transformation will be applied to approximate normal distribution as appropriate. Repeated measurements, mixed models will be made for analysis of the continuous variables with multiple measurements.

Missing data

In case of missingness greater than 5% for the primary endpoint, multiple imputations by chained equations will be applied as sensitivity analysis with generation of 10 individual data sets.

For other endpoints, first a worst case and best-case analysis will be made and if significant differences, multiple imputations will be performed.

Analysis of survival data and other outcomes

Kaplan-Meier curves for each group will be graphically displayed and compared by the log-rank test. Further multivariable Cox proportional hazard models will be applied to assess differences in time to death between treatment groups. These models will sequentially be adjusted for the interaction between treatment allocation, and each of the predefined covariates. Further, models stratified by individual components of the predefined covariates will be made as hypothesis generating. Any changes from the pre-specified analysis plan will be reported.

Outcomes will be evaluated using univariable and multivariable logistic regression models after examining assumptions of linearity and proportionality. Hazard ratios (HRs) and Odds ratios (ORs) with corresponding two-sided 95% confidence intervals (CI) will be presented.

Multivariable models are adjusted for:

*Admission SBP (quartiles), age, sex, body mass index, LVEF at admission (>50, 40-50, <40), NT-proBNP (above/below median), eGFR, supraventricular arrhythmia at admission, comorbidities (history of heart failure, obstructive pulmonary disease), systemic congested (Yes/no, defined as at least 3 kg above ideal weight at admission).*

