The covariates are pre specified before analyses and were chosen based on a consensus of the steering committee based on experiences from previous trials of AHF. Interaction between covariates will be tested by adding the interaction term to the models.

Subgroup analysis

Subgroup analysis will be made for all the prespecified covariates. Interaction with treatment effect will be tested for each covariate and a forest plot will be plotted.

Two-sided p-value of less than 0.05 is considered statistically significant. All analyses will be conducted in the modified intention-to-treat (ITT) (all randomized patients fulfilling the inclusion criteria and excluding those, which consent have been withdrawn) population. Statistical analyses are performed using the SAS statistical software, version 9.4 (SAS Institute, Cary, NC) and in R version 3.3.3 (R Foundation for Statistical Computing, Vienna, Austria).

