## 13.6 Reporting Procedures for All Adverse Events

All adverse events occurring after inclusion observed by the investigator or reported by the subject (whether attributed to investigational product), will be reported on the case report form. Medically significant adverse events considered related to the investigational product by the investigator or the sponsor will be followed until resolved or considered stable.

The following attributes must be assigned by the investigator: description; dates of onset and resolution; severity; assessment of relatedness to investigational product, other suspect drug, or device, and action taken. The investigator may be asked to provide follow-up information.

It will be left to an investigator’s clinical judgment as to whether an adverse event is of sufficient severity to require a subject’s removal from treatment. A subject may also withdraw voluntarily from treatment because of what he or she perceives as an intolerable adverse event. If either of these situations arises, the subject must undergo an end-of-study assessment and be given appropriate care under medical supervision until symptoms cease or the condition becomes stable. If the subject was permanently withdrawn from the study or investigational product due to a serious adverse event, this information must be included in either the initial or follow-up Serious Adverse Event Report Form or the End of Study Case Report Form. Data on deaths and hospitalizations will be collected until study termination.

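### Recruiting until 122 patients have an observed 24-hour ReDS value protects power, but leaves the primary comparison in effect a completers analysis that does not fit the declared modified ITT population

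*Protocol*

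**What the plan says.** The primary outcome in Section 7.1 is "Pulmonary parenchymal fluid content measured by ReDS after 24 hours preceded by 10 minutes without oxygen-supplementation". Section 8 sizes the trial on one value per patient: "To have 90 % power to find a difference of 4 % in lung fluid content (change from 39.8% to 35.8"%), with an SD of 6.8, giving 61 per group. It expects minimal dropouts and adds no allowance for them. It then sets the recruitment rule: "We will include patients until we have reached the estimated sample size without any missing values in the primary outcome", with the stated aim of being able to conclude on the primary hypothesis.

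The Statistical analyses plan (Section 12) bears on the same outcome in four places:

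- Continuous variables are compared with the t-test.
- Mixed models are planned for continuous variables with multiple measurements. ReDS is not named there.
- On missing data: "In case of missingness greater than 5% for the primary endpoint, multiple imputations by chained equations will be applied as sensitivity analysis".
- On the population: "All analyses will be conducted in the modified intention-to-treat (ITT"), defined as all randomised patients who fulfil the inclusion criteria, less those whose consent has been withdrawn. A missing ReDS value is not a ground for exclusion.

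On early stopping, Section 5.1 lets the treating physician end the intervention phase prematurely. Section 8.1 says all included patients continue to day 30 or death. Section 13.6 says of patients removed from, or withdrawing from, treatment because of an adverse event: "If either of these situations arises, the subject must undergo an end-of-study assessment". Appendix 4 schedules the 24-hour ReDS without exemption.

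**The concern.** The recruitment rule treats a missing 24-hour reading as a shortfall in numbers. The loss may instead carry information. A patient may lack a valid reading through death or intubation before 24 hours, an early stop, or inability to spend 10 minutes without oxygen. Each of these is plausibly related to congestion, and early stops are plausibly related to arm. The device alarms below 88% saturation, which is 2 points below the restrictive target and 8 below the liberal one.

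If wetter patients are lost more often in one arm, that arm looks drier than it is. If it is the restrictive arm, the error favours the trial's hypothesis. Recruiting further patients who are subject to the same losses reproduces the same selection. What is at stake is whether the headline result compares the randomised groups or only those of their members who could be measured.

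**Working it through.** **1. The plan's own figure.** Inputs are a difference of 4, SD 6.8 and 90% power (Section 8), with a two-sided 5% level (Sections 8 and 12).

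n per arm = 2 × (1.960 + 1.282)² × 6.8² / 4² = 60.7, rounded up to 61, so 122 in total. The stated figure is reproduced. Power at 61 per arm is 90.1% by the normal formula and 89.7% by the exact t-test. The figure matches a two-sample comparison of a single 24-hour value.

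**2. What the top-up does for power.** To end with 122 observed values at an assumed missing share m, the number randomised is 122 / (1 − m): 125 at 2%, 129 at 5%, 136 at 10%. Without the top-up, 5% missing leaves about 58 per arm and 88.1% power by t-test. The rule therefore does what it can do for power.

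**3. What it does for bias.** Let p be the missing share in an arm and d the amount by which its missing patients are wetter, on average, than its observed ones. The full-arm mean is (1 − p) × observed mean + p × (observed mean + d), which is the observed mean + p × d. Each observed mean is thus too low by p × d. With the same d in both arms, the difference between arms is biased by (p1 − p0) × d, in favour of the arm that loses more. The number recruited does not appear in this expression, so the top-up cannot change it.

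**4. Size.** The protocol gives neither p nor d. All missing shares below are assumptions, with d = 6.8 (1 SD). The standard error at 61 per arm is 6.8 × √(2/61) = 1.23. Type I error is Φ(−1.96 − b/SE) + Φ(−1.96 + b/SE), where b is the bias.

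| Missing, arm 1 v arm 0 | Bias (points) | Share of the 4-point target | Type I error |
| --- | --- | --- | --- |
| 5% v 5% | 0 | 0% | 5.0% |
| 3% v 2% | 0.07 | 2% | 5.0% |
| 8% v 4% | 0.27 | 7% | 5.6% |
| 12% v 4% | 0.54 | 14% | 7.3% |
| 20% v 5% | 1.02 | 26% | 13% |

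A second model, in which the most severe fraction of each arm has no value and severity correlates with ReDS at 0.3 to 1, gives a similar range: 0.23 to 0.76 points for 2% v 8% missing, and 0.34 to 1.13 points for 5% v 15%.

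**5. The 5% rule.** Counted over all randomised patients, with 122 observed, six missing give 6/128 = 4.7% and seven give 7/129 = 5.4%. The imputation trigger is therefore met at the seventh missing patient. Counted over the 122 observed, missingness is 0% by construction. The protocol does not say which denominator applies.

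**The case against.** The strongest reply is that Section 8 contains only a recruitment rule. It removes nobody from the analysis. Section 12 keeps randomised patients in the modified ITT set, and Section 8.1 keeps them in follow-up to day 30. This stands. A reader might infer that patients without a value are replaced in the analysis set, or that the rule removes the sickest, but the protocol says neither. The completers character comes from the rule combined with the t-test and the secondary place given to imputation.

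A reader might also infer that the rule disables the 5% trigger. That needs a denominator of 122 completers, which the protocol never states. The two provisions are unreconciled, not strictly contradictory.

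The mixed-model sentence could cover ReDS, which is measured at baseline and 24 hours, and such a model can use patients who have only a baseline reading. This is the best point on the other side. However, the sentence is not tied to ReDS, the primary outcome is defined at 24 hours alone, and the sizing matches a two-sample test.

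Section 13.6 could be read as ending measurement after early stopping. It says that death and hospitalisation data are collected to study termination, but it does not cancel the 24-hour ReDS. The position is ambiguous, no more.

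Finally, the bias is assumed throughout. The protocol expects minimal dropouts, its mortality figure of at least 20% covers 30 days and not 24 hours, and Section 5.1 notes that most such patients were off oxygen after 24 hours. All of this stands, and it limits what can be said about size.

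**Conclusion.** The point holds in a limited form. The arithmetic behind 122 is correct, and recruiting to 122 observed values preserves power at about 90%. It does not by itself allow a valid conclusion on the primary hypothesis. As written, the primary comparison rests on patients with a 24-hour value, and this does not fit the modified ITT population declared for all analyses.

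The bias needs two conditions together: losses that differ between arms, or are differently selective, and losses that are related to congestion. Under the assumed rates with d = 6.8 it runs from 0.27 to 1.02 points, or 7% to 26% of the target effect. It is near zero if losses are minimal, or balanced and equally selective. The protocol gives no figure that decides between these cases, which is a reason to fix the method before the data are seen.

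**What to change.** 1. **Name the primary analysis of ReDS.** Use a baseline-constrained mixed model, or multiple imputation that includes baseline ReDS and arm, in all modified ITT patients whatever the missing share. State that the 5% rule, if kept as a trigger for a further sensitivity analysis, is counted over all randomised patients. Add a sensitivity analysis for death before 24 hours. Baseline ReDS is already scheduled (Section 9 and Appendix 4). The model corrects only for missingness explained by baseline ReDS and arm, so the sensitivity analysis is still needed.
2. **State that the 24-hour ReDS is taken in every patient still in hospital**, including those whose intervention was stopped early, and reconcile Sections 5.1, 8.1 and 13.6 and Appendix 4 on this. Flag any reading not preceded by the off-oxygen period. Whether a patient can undergo that period remains a clinical matter for the trial team.
3. **Delete the claim that recruiting to 122 observed values ensures a conclusion.** The top-up may stay as a power safeguard, with the numbers randomised and missing reported by arm. Closing at 122 randomised instead would remove no bias and would cost some power.

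The cost is a protocol wording change, a little more analysis work and a few extra flagged readings. Baseline adjustment should more than offset a small loss of observed values. At 58 per arm, power is 88.1% by t-test, 90.9% if baseline and 24-hour ReDS correlate at 0.3, and 95.2% at 0.5. Both correlations are assumptions. Readings not taken at 24 hours cannot be recovered later, so item 2 is the urgent one.

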## 8.1 Expected enrollment

Our pilot-study of patients admitted with acute dyspnea from Bispebjerg University Hospital, we screened 707 patients during 20.5 months inclusion [29, 30]. Applying the current study criteria in that dataset, we find an incidence of eligible patients of 2-5 patients per week. We choose a conservative estimate of including approximately 1 patient per week per site. We expect to include at 2 centers, thus including expected duration of 1 year (we expect a slower inclusion in the initial phase of the study).

All included patients will continue in the study until 30 days after inclusion and/or death.

# 9. Pre-defined study-procedures

#### At inclusion and after 24 hours the patients will have a physical examination where the pulmonary respiratory sounds will be recorded as part of the evaluation of the degree of cardiac incompensation.

#### Echocardiographic parameters

At all sites, an advanced transthoracic echocardiography (TTE) will be performed at admission prior to start of intervention and again after 24 hours. Echocardiography is part of routine monitoring in these patients and is not deemed to expose the patients to excess risk. The first TTE will be performed prior to titration towards the allocated target SpO2. The primary measured outcome will be the change in longitudinal peak systolic strain (%) measured between identical TTE image acquisitions obtained in the same individual. Secondary outcome measures include the acquisition of the remaining TTE 2D and 3D systolic and diastolic strain parameters (i.e. time to peak strain, systolic and diastolic strain rates, displacements, velocities, torsion) and traditional TTE measures as well such as ventricular volumetry and function, stroke volume derived from the velocity time integral of the left ventricular outflow tract, tissue doppler and mitral valve inflow patterns to assess diastolic function, right ventricular fractional area change and tricuspid annular plane systolic excursion [31].

#### Remote Dielectric Sensing (ReDS)

Lung fluid content will be assessed noninvasively at admission and after 24 hours by the remote dielectric sensing (ReDS) device (Sensible Medical, Netanya, Israel). ReDS is an FDA-approved, wearable device developed by Sensible Medical Innovations that allows clinicians and other health care providers to quickly and accurately measure lung fluid in patients, noninvasively.

The lung fluid content is measured within the mid-region of the right lung. The measurement is presented as the percentage of the lung volume composed of fluid, (normal values for non-congested people is 20%-35% of fluid content) [25].

Using the ReDS technology in our study will seek to directly measure the degree of pulmonary congestion in acute heart failure patients and assess whether the effect of oxygen-level will be influenced by degree of pulmonary congestion at various points of care.

#### Carbon monoxide rebreathing method

The method is based on the dilution principle, where carbon monoxide binds with great affinity to circulating Hemoglobin molecules. Carbon monoxide is inhaled for 6 minutes and the increase in carboxyhemoglobin from before to after inhalation can be used to calculate the hemoglobin mass. Carboxyhemoglobin is measured at the start at time 0 and again after 8 minutes from the end of the rebreathing method (+14 min from the start). From the Hemoglobin mass, Hemoglobin and hematocrit, the total blood volume, plasma volume and erythrocyte volume can be calculated [32]. The amount of carbon monoxide that will be absorbed during the experiment is small (1.2 ml kg-1) and will only increase the level of carbon monoxide in the blood by a maximum of 12%, which is not associated with risks or discomfort [33]. The level of carbon monoxide after rebreathing is similar to the levels seen by living in a big city for 12-48 hours. Exercise capacity and circulating carbon monoxide levels in the blood return to normal levels within approx. 12 hours.

# 10. ETHICAL CONSIDERATIONS

The trial will be conducted in accordance with national legislation on medical research involving humans. The Danish legislation requires consent the patients prior to inclusion. The investigators will be responsible for application to the ethical committee and for adherence to national legislation on subject enrolment in the trial.

### 10.1 ETHICAL JUSTIFICATION

The participation and interventions in the trial will not interfere with or delay diagnostics, therapeutic procedures or medication

Potential benefits and potential harms

Interventions in this trial are routine treatments used for these patients for more than 100 years. The profile and side effects of oxygen are well-known and considered to be insignificant in the doses proposed in this trial. Details about the potential benefits of the intervention are provided in the background section.

Most importantly, if the patient is not included in this trial, the same doses of oxygen will be given to the patients in a non-systematically way as part of guideline-recommended treatment. As described in the background-section, there is clinical equipoise of which strategy that is superior in the acute setting.

Research in acute heart failure with pulmonary congestion

Research in pulmonary edema is ethically challenging for two reasons: 1) Patients can be acutely affected by dyspnea and 2) treatment must be administered within minutes. Despite these challenges, there is an ongoing need to conduct research in this patient-population to improve outcome, which is also recommended in international guidelines, such as the Declaration of Helsinki [34].

The ethical justifications for interventions in the trial are:

1. Knowledge of the optimal oxygenation therapy of patients in acute heart failure is limited and there is clinical equipoise regarding optimal oxygenation strategy.
2. The trial interventions are expected to be of minimal risk to the patient and are within current treatment guidelines, common clinical practice, and local protocols. The patients will, in other words, exclusively be presented for treatments, that are already part of the guidelines-recommended standard-of-care.
3. Increased knowledge of therapeutic potential of the intervention would increase the scientific knowledge of the condition of the individual and other patients with AHF and/or pulmonary edema, without exposing the patients to significant risk.
4. Any relevant expressed objections to participation in clinical trials of the person known to the researcher will be respected, and study participation will be terminated.
5. Inclusion in the trial may be of value to the individual patient but is valuable to the group of patients with acute heart failure in general, since further knowledge is needed to continue optimization of the interventions for this condition.

## 9.2 Informed consent

The trial-protocol will be sent for approval by the ethics committee.

Consent will be obtained from the patient when he/she is deemed capable for the information and will be asked for a written informed consent (paper or in REDcap).

At any time, if the patient asks to be taken out of the trial, this will be respected. If a patient denies future participation in the trial, no additional data will be collected but all data collected up until the point of withdrawal will be included consistent with Danish law.

Information

Informed consent will include information that the hospital uses the best evidence-based therapy to relieve dyspnea for this patient. The patient is told that two equal treatment options exist, and we will give one of them after randomization, provided there are no contraindications or exclusion criteria. On the possible inclusion in the trial, every measure possible will be taken to ensure a quiet environment for the information.

Insurance

The patients in the study are covered by the Danish patient insurance.

# 11. Monitoring

### 11.1 Good Clinical Practice monitoring

The trial will not be monitored for Good Clinical Practice, since this is not required in non-drug trials. However, the GCP standards will be followed.

## 11.2 Access to Source Data and Documentation

The principal investigator will permit monitoring, audits, reviews of ethical committees and regulatory authorities’ direct access to source data, blinded to treatment allocation. Informed consent includes an accept of the data access in the study’s eCRF for the principal investigator and further the Danish Medicines Agency for quality control. Information on written consent for both patients and nearest relatives includes information on data access.

